### Treatment regimens

#### Control group

Control group participants are provided with general health advice in the form of a standard British Heart Foundation information leaflet after visit 1, and are returned to standard care delivered by their GP. The information leaflet entitled ‘*Put Your Heart into Walking*’ describes walking as a fitness activity to keep your heart healthy [28].

#### Intervention group

Participants randomised to the intervention group receive the standard information leaflet after visit 1 and are invited to attend the PACES education programme which comprises two group-based structured education sessions.

Development of the intervention followed an iterative pathway comprising various stages of designing, testing and refining the education programme through the use of informant groups [29]. The theoretical underpinnings employed and processes used to inform the behaviour-change techniques in the programme include those recommended by Michie et al*.* [26], the NICE 2014 guidelines [25] and the behaviour-change taxonomy [26]. The COM-B system has been employed as an overarching model for understanding the factors underlying behaviour and behavioural change; namely, capability, motivation and opportunity [30]. This structured approach ensures that all aspects of the programme have a rationale and an aim.

The importance of tailoring interventions to meet the needs of the targeted clinical population has been recognised. All development stages, therefore, comprised of extensive patient and public involvement (PPI) work with health care professionals based in primary care and cardiac rehabilitation and with cardiac patients. Both groups worked closely with the development team to create a bespoke group-based education programme. The education sessions are 2.5 h in duration and delivered by two trained facilitators approximately 2 weeks apart. Sessions are delivered in a facilitative style that encourages participation with the use of reflective questioning and problem-solving activities to promote engagement and build self-efficacy. The PACES programme content is underpinned by an integrated theoretical framework encouraging the adoption and maintenance of healthy behaviours and lifestyle; specifically, increasing physical activity levels through daily walking activity, along with diet. The following topics are covered:What is CHD?Risks and how to reduce these risks to maintain a healthy heartThe benefits of physical activity on CHDThe importance of medication and healthy eatingImproving confidence and personal motivation to increase physical activityRecognition of the personal barriers and facilitators to physical activityHow to assess and goal plan physical activity using a self-monitoring tool (the participant is given a pedometer and activity diary to help with self-monitoring)

All attendees subsequently receive physical activity-related motivational reinforcement via text-message support. The participants receive 82 physical-activity-related text messages at different weekly frequencies following the second education session until the 12-month follow-up assessment. The text messages are non-interactive and are designed to be motivational in nature. The text-message support used is a validated package of messages designed and shown to be effective in the prevention of recurrent cardiovascular events [31, 32]. The current study is a pragmatic trial, and the target is to attend the education within 2 months of recruitment. However, this will not always be possible. A sensitivity analysis will be performed to take this into account.

##### Facilitator recruitment and training

Potential facilitators initially responded to an advertisement or attended a recruitment event after which they underwent shortlisting according to certain criteria necessary to the position (a registered health care professional or a professional in the field of health, health promotion or sports science, knowledge of CHD, experience working face-to-face with the general public and experience of group working).

All recruited facilitators attended an initial 2-day training course (session 1 general facilitator training and session 2 study-specific training, 15 h training in total) to ensure that they understood the theories and philosophy that underpin the PACES programme. The training course also covered the PACES curriculum content and ensured familiarisation with the teaching resources used within it. All facilitators were provided with a curriculum and resource pack to support a successful delivery and give them the opportunity to plan ahead of each session. The facilitators then delivered a ‘have a go session’ before the study started to enable them to practise delivery to a volunteer cardiac patient group. These practice sessions were observed by a member of the training team and feedback and further training were provided to the facilitators as necessary. Continued peer support is provided to the facilitators and self-reflection and peer reflection after every session is encouraged.

##### Intervention fidelity

An intervention fidelity tool has been developed to monitor and report adherence in a predetermined sample of the programmes delivered. It includes an ‘adherence measure’ to capture delivery (mode of delivery/duration/content) and use of resources (materials/activities) and a structured observation tool to assess facilitator delivery of prescribed behaviours and behaviour-change techniques [33]. The observation tool also includes an assessment of ‘talk time’ as a measure of quality of delivery [34]. Observation of delivery is being undertaken by trained observers who have been assessed as reliable in the use of the structured observation tool [33].

### Study outcomes

All clinical visits are run by trained individuals, predominantly research nurses and health care assistants from the University Hospitals of Leicester. All research staff have been trained in the study procedures and follow standard operating procedures (SOPs) when doing so. Written informed consent is obtained by a trained research nurse before any trial activities take place. Outcome data are collected at three time points – baseline, 6 months (postal) and 12 months (Table 1). Participants and their GPs are sent a letter with details of selected clinical results after the baseline and 12-month clinic visits.

The following demographic and medical history data are recorded for each participant: date of birth, gender, ethnic background, family history, employment status, smoking status, alcohol status and details of any relevant history of disease, medications, or relevant surgical interventions.

### Primary outcome

The primary outcome measure is change in objectively measured ambulatory activity from baseline to 12 months using the GENEActiv wrist-worn, tri-axial accelerometer (GENEActiv model 1.1, ActivInsights Ltd., Kimbolton, UK) with a dynamic range of ± 8 g, where g is equal to the earth’s gravitational pull. Increasing physical activity is an important behaviour to adopt after a cardiac event illustrating why objective ambulatory activity has been selected as the primary outcome. Participants are asked to wear the GENEActiv accelerometer on their non-dominant wrist for eight consecutive days (24 h) (wearing the monitor from the date of the assessment visit or from a specified date when sent in the 6-month postal follow-up). The accelerometer is configured to collect data at 100 Hz and records total physical activity, which includes light, moderate, vigorous and moderate to vigorous physical activity (MVPA), sedentary behaviour and sleep in milli-gravitational units (mg). Participants are also asked to complete a log whilst wearing the monitor to provide their waking hours and wear-time information. An appropriately trained individual instructs the participant on correct placement of the monitor using the SOPs. Participants are given a stamped addressed envelope to return the monitor once completed. Upon return the data are downloaded to a computer using the software supplied by the manufacturer and are then ready for analysis. The accelerometers are processed by staff blinded to the intervention group allocation.

### Secondary outcomes

#### Anthropometric measures

Body mass is measured using the bioelectrical impedance Tanita Scales BC-418-MA (Tanita Corporation, Tokyo, Japan) and stretch stature is measured using a portable stadiometer (Holtain, Crymych, UK). Body mass (kg) and stretch stature (cm) values are used to calculate Body Mass Index (BMI) as body mass (kg) divided by height (m) squared. Waist (approximately 1 cm above the iliac crest) and hip (widest area around the gluteus maximus) circumferences are recorded and waist:hip ratio (WHR) calculated. These measurements are included as an indicator of abdominal obesity [35].

#### Cardiovascular measures

Blood pressure and resting heart rate are obtained after participants have been seated for at least 5 min using the Omron HEM-907 Digital Upper Arm Cuff Blood Pressure Monitor (Omron Corporation, Kyoto, Japan). Participants remain seated with their left arm supported whilst the measurement is taken. Blood pressure is taken three times; the first measurement is discarded and a mean of the following two measurements is reported.

#### Functional walking measurement

The Incremental Shuttle Walk Test (ISWT) is used as a screening measure, as well as a secondary outcome measure, as it reflects walking ability, an important measure of daily living in these clinical patients. The ISWT has been validated against VO_2_ max and VO_2_ peak in clinical populations [36, 37]. A linear relationship is reported between functional capacity and the number of shuttles completed in a clinical population [37].

The ISWT involves a patient walking consecutive 10-m shuttles in time with an audible beep that becomes progressively faster, until they are no longer able to maintain that pace. The test has a total of 12 levels lasting 1 min each (total distance 1020 m). Participants perform a practice ISWT to minimise the influence of learning effects and are then asked to walk for as long as possible until reaching test termination criteria whilst the assessor records the total number of shuttles performed [38, 39]. The participant remains in the clinical area for at least 15 min following the test where measures of blood pressure, heart rate, oxygen saturation, rating of perceived exertion (RPE Borg Scale) and breathlessness (the modified Borg Dyspnoea Scale) are taken. The participant must achieve level 3 or above on the ISWT (120 m), and, if they are not able to achieve this, they are excluded from the study and directed back into cardiac rehabilitation (a letter is sent to the cardiac rehabilitation team suggesting referral; their GP is sent a copy of this letter) as a process of good practice [27]. This test is conducted by a basic life support (BLS)- or immediate life support (ILS)-trained member of the study team, experienced in conducting the ISWT. If the ISWT is being conducted by a BLS-trained individual, an ILS-trained member of staff is also available within the PACES clinic.

#### Questionnaire data

##### Recent Physical Activity Questionnaire (RPAQ)

The RPAQ is designed to explore day-to-day physical activity levels in the past 4 weeks. The questionnaire is divided into three sections: (1) physical activity patterns in and around the house, (2) travel to work and work activities and (3) recreational activities. This questionnaire has been validated against previous studies and is comparable when estimating energy expenditure and MVPA [40, 41].

##### Hospital Anxiety and Depression Scale (HADS)

The HADS is a validated scale measuring the severity of symptoms of anxiety and depression. It comprises 14 statements, of which seven relate to anxiety and seven relate to depression [42]. Each statement has an option of four responses scored from 0 to 3. Upon completion, selected scores are totalled and reported for anxiety and depression individually [42].

##### EuroQoL EQ-5D-5L

The EQ-5D assesses health-related quality of life and provides useful data for health economic analyses. The EQ-5D-5L is a validated measure of health status and has been validated specifically in chronic conditions, such as cardiovascular disease. The EQ-5D-5L has five quality of life dimensions (mobility, self-care, usual activities, pain/discomfort and anxiety/depression) which are all coded between 1 and 5 [43, 44].

##### Jenkins Self-efficacy for Exercise Expectations Scale

This validated self-efficacy scale measures ability to continue exercising in the face of nine barriers to exercise [45]. These barriers are specifically relating to when you are bothered by the weather, boredom, pain, exercising alone, lack of enjoyment, busyness, tiredness, stress and depression.

##### MacNew Heart Disease health-related quality of life instrument

The MacNew Heart Disease health-related quality of life instrument is a validated questionnaire designed to appraise how CHD affects emotional, physical and social functioning along with daily activity [46]. The MacNew is a 27-item questionnaire which is divided into the three factors of social functioning, physical functioning and emotional functioning [47, 48].

##### Morningness-Eveningness Questionnaire

The Morningness-Eveningness questionnaire is a 19-item self-assessment questionnaire that determines morningness-eveningness in human circadian rhythms (chronotype) [49, 50]. Disruption of circadian rhythms is reported as a significant risk factor for many cardiovascular diseases [51].

#### Laboratory tests – blood samples

Venous blood samples are taken during the baseline and follow-up clinics and sent for analysis of full lipid profile and HbA1c in accredited laboratories at University Hospitals of Leicester. The samples are analysed in accordance with the laboratory’s SOPs. All laboratory results are reviewed and the reports signed by the study medic who records in the case report form (CRF) whether they are normal, abnormal but not clinically significant, or abnormal. If abnormal, a letter is sent to the participant’s GP.

##### Exploratory endpoint

The feasibility for the measurement of biomarkers of inflammation, proteomics, metabolomics and novel markers of cardiovascular health will be determined as new knowledge and methods for assaying evolve. When providing informed consent, participants have the option to consent to the storage of their samples. If consent is obtained, additional samples are obtained, centrifuged at the point of collection, and stored as plasma and serum samples in a − 80 °C freezer using standardised stable methodology within the Leicester Diabetes Centre.

### Sample size

The PACES study power calculation was based on the primary outcome of change from baseline to 12 months of average daily physical activity, as quantified by the Euclidean norm minus one (ENMO) method measured in milli-gravitational units (mg). This is the main measure of activity derived from the GENEActiv activity monitor. In order to detect a minimum clinically significant difference of 2.1 mg, which is equivalent to an overall increase in physical activity volume of approximately 30 min of light walking at 4 km/h, assuming a standard deviation (SD) of 5.3 mg [52], a power of 80% and significance level of 5%, the sample size requires 202 participants. To allow for 20% loss to follow-up and 10% non-compliance of the activity monitor, 290 participants will be recruited to this trial (145 in each group).

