### Randomisation

Upon completion of visit 1, participants are randomised using a 1:1 block design and stratified by gender (men; women) and ethnicity (White European; other) to receive either standard management in primary care or to a complex intervention with group-based structured education and text-message support. An exception is made for people living in the same household, where in the unlikely event of this occurring the second person is not randomised but is allocated to the same arm as the first person. This is to prevent contamination between people living in the same household but randomised to different arms. The randomisation schedule and list was developed by an independent statistician and allocation of randomisation is carried out by a researcher independent of the team. Participants are informed of their randomisation allocation once visit 1 is completed, ahead of their 6 and 12 months’ follow-ups. As the intervention is a group education programme the participants cannot be blinded to the randomisation. The research nurses collecting the follow-up data are not informed of the randomisation of the participant but it is possible that the information is passed onto them by the participant.

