#### Primary outcome data processing and data analysis

The primary outcome, change in average daily physical activity measured by the GENEActiv in mg from baseline to 12 months will be processed ahead of analysis. The GENEActiv data are downloaded using GENEActiv software version 3.1 and stored as raw bin files by assessment time point. These files will be analysed using the most up to date R-package, GGIR, using the version that is most up to date when analysis happens [53, 54]. Automatic calibration using local gravity as a reference, recognition of sustained abnormally high values, calculation of the average resultant vector magnitude, corrected for gravity and expressed as ENMO in mg averaged over 1-s epochs [54]. Files will be excluded from analyses if post-calibration error was greater than 0.01 g or fewer than 4 days of 16 h of wear-time were recorded by the monitor. Non-wear is estimated based on the SD and value range of each axis, calculated for 60-min windows with 15-min moving increments. If for at least two out of the three axes the SD is less than 13 mg or the value range is less than 50 mg the time window is classified as non-wear. Output variables will include overall physical activity and time spent inactive, in light physical activity and in moderate-to-vigorous physical activity.

After processing the primary outcome data the treatment arms will be compared using linear regression modelling with (1) a binary indicator for randomisation group as the explanatory variable, (2) terms for the stratification factors as confounders and (3) adjustment for the change from baseline in accelerometer wear-time and baseline average daily physical activity. Apart from those living in the same household, individuals are stratified by gender (men; women) and ethnicity (White European; other). Sensitivity analyses will include a per-protocol analysis, an intention-to-treat analysis where missing data are imputed using multiple imputation or another suitable method, and analyses with the intervention arm restricted to participants who attend the education within 2 months of recruitment. Interaction effects will be fitted between intervention arm and gender (male vs. female), and ethnicity (White European vs. other). If the interaction term is statistically significant at the 10% level then stratified analyses will be performed for that factor using the same model as the primary analyses.

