Secondary outcomes will be analysed using similar methods as the main analysis, with an appropriate model selected dependent on the distribution of the outcome. The results of all comparative analyses will be presented with 95% confidence intervals and statistical significance for main effects will be assessed at the 5% level. All *p* values shown will be two-sided. Statistical significance for interaction effects will be assessed at the 10% level. Any deviation(s) from the original statistical analysis plan will be described and justified in the final report.

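### The sample size and the stated primary regression make no allowance for correlation within education groups, which exist in the intervention arm only

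*Protocol article*

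**What the plan says.** All places are in the protocol article.

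- **Randomisation:** allocation is by individual: "participants are randomised using a 1:1 block design and stratified by gender (men; women) and ethnicity (White European; other". A second member of a household goes to the same arm as the first.
- **Control group:** a leaflet, then usual care from the GP. Nothing is delivered in groups.
- **Intervention group:** participants are "invited to attend the PACES education programme which comprises two group-based structured education sessions". Each session lasts 2.5 h, is led by two facilitators and is built on participation and problem-solving. The number taught together is not given.
- **Sample size:** the target is given as "In order to detect a minimum clinically significant difference of 2.1 mg"; the spread is fixed by "assuming a standard deviation (SD) of 5.3 mg"; and the result is stated as "a power of 80% and significance level of 5%, the sample size requires 202 participants". Attrition is then added: "To allow for 20% loss to follow-up and 10% non-compliance of the activity monitor, 290 participants will be recruited to this trial (145 in each" (the split is by arm). No group size, ICC or design effect enters.
- **Primary outcome data processing and data analysis:** "the treatment arms will be compared using linear regression modelling", where the terms are arm, the stratification factors, change in wear-time and baseline activity. The sensitivity analyses listed are per-protocol, imputed intention-to-treat, and the intervention arm restricted to those who attend education within 2 months. None concerns education group or facilitator. On tests, "values shown will be two-sided".

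**The concern.** This is a partially nested design, with independent controls on one side and participants who share a room, a discussion and a pair of facilitators on the other. The protocol itself treats delivery as something that can vary. Its Intervention fidelity section monitors facilitator behaviours and talk time, and the Discussion names consistency among facilitators as an aim. Some correlation in 12-month activity within a group is therefore plausible, although the article gives no evidence of its size.

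A positive correlation makes the intervention-arm mean less precise than a regression with independent errors reports. The confidence interval for the primary comparison would then be too narrow, and the error runs towards declaring a difference that is not there. The same correlation erodes the power stated for 202 evaluable participants.

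**Working it through.** **Inputs from the article.** Difference δ = 2.1 mg, SD σ = 5.3 mg, power 80%, two-sided 5%, 1:1 allocation, 20% loss plus 10% monitor non-compliance, 290 recruited.

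**Inputs assumed.** The number analysed per education group, m, and the ICC. The article gives neither.

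**Step 1: reproduce 202.**
- Normal approximation: n per arm = 2(1.96 + 0.8416)² × 5.3² / 2.1² = 99.99, so 100.
- Two-sample t-test: 100.96, so 101 per arm and 202 in total, exactly the stated figure. Its power at 101 per arm is 80.0%.
- Attrition: 202 / 0.70 = 288.6, consistent with 290.

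The arithmetic is right for independent participants. The implied design effect is 1, and 202 has no slack.

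**Step 2: clustering in one arm only.**
- Design effect in the intervention arm: DE = 1 + (m − 1) × ICC.
- Variance of the difference with n per arm: σ²(1 + DE)/n, against 2σ²/n under independence.
- Ratio of true to assumed standard error: k = √((1 + DE)/2).
- Actual type I error of the unadjusted test: 2[1 − Φ(1.96/k)].
- Power of a valid test: Φ(δ/(k·SE₀) − 1.96), where SE₀ = 5.3 × √(2/101) = 0.7458, so δ/SE₀ = 2.816.

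**Step 3: which m.** The design effect depends on the number analysed, not the number invited. The primary analysis is complete-case, so if 8 are assigned to a group and 30% are lost, 8 × 0.70 = 5.6 are analysed. The table runs from 5.6 to 12.

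| Analysed per group | ICC | DE | k | Type I error | Power, 101 per arm |
|---|---|---|---|---|---|
| 5.6 | 0.01 | 1.046 | 1.011 | 5.3% | 79.5% |
| 5.6 | 0.02 | 1.092 | 1.023 | 5.5% | 78.6% |
| 5.6 | 0.05 | 1.230 | 1.056 | 6.3% | 76.0% |
| 8 | 0.01 | 1.070 | 1.017 | 5.4% | 79.0% |
| 8 | 0.02 | 1.140 | 1.034 | 5.8% | 77.7% |
| 8 | 0.05 | 1.350 | 1.084 | 7.1% | 73.8% |
| 12 | 0.01 | 1.110 | 1.027 | 5.6% | 78.3% |
| 12 | 0.02 | 1.220 | 1.054 | 6.3% | 76.2% |
| 12 | 0.05 | 1.550 | 1.129 | 8.3% | 70.3% |

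These use the normal approximation, which gives 80.4% at ICC 0, so the loss in each row is measured from 80.4%. They also treat every analysed intervention participant as belonging to a group. Those who never attended have none, which shrinks the effect; unequal group sizes would enlarge it somewhat.

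**Step 4: possible offsets to the power loss.**
- *Baseline adjustment.* The model adjusts for baseline activity, and the sample size takes no credit for it. The article does not say whether 5.3 mg is already a residual SD. If it is not, the cut in residual variance that cancels the clustering is 1 − 2/(1 + DE): 14.9% at m = 8 and ICC 0.05, and 21.6% at m = 12 and ICC 0.05.
- *Sequential attrition.* If the two allowances multiply, 290 × 0.8 × 0.9 = 208.8, or about 104 evaluable per arm. At m = 8 and ICC 0.01, power is then 80.2%.

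Both bear on power only. Type I error depends on k, which neither changes at a given m and ICC.

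**The case against.** The strongest reply is that the harm is conditional. With an ICC of zero nothing changes, and with small analysed groups and an ICC of 0.01 the effect is trivial. A reader might infer from the design that the standard errors are wrong and that 80% power will not be delivered. The article does not support that as fact: it supplies no ICC or group size, and the two offsets above could bring power back to 80%. Nor does it support the inference that 202 is miscalculated or that 290 must be raised. This part of the objection stands, and the point is worded accordingly.

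A second reply is that this is a journal article, that it refers to a statistical analysis plan not shown here, and that linear regression does not by itself fix the variance estimator, so cluster-robust errors would be compatible with the text. That is fair as far as it goes, and the separate plan may deal with the matter. But the article sets the sample size on independence, and it names the model, its covariates and its sensitivity analyses. What is questioned is that stated specification.

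Third, a random group effect would be estimated from few groups: about 101 / 8 ≈ 13 at 8 analysed per group. This is a reason for small-sample corrections and for leaving the choice of method open. It does not justify assuming independence.

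**Conclusion.** The point holds in conditional form. Neither the sample size nor the stated primary regression allows for correlation within education groups. If that correlation is positive, the unadjusted standard error is too small and the test exceeds its nominal 5%; other inputs equal, power at 202 evaluable is below 80%. Over 5.6 to 12 analysed per group and ICC 0.01 to 0.05, all assumed, type I error is about 5.3% to 8.3% and power about 79.5% to 70%.

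The analysis half is the firmer. The power half may be offset by baseline adjustment or by a slightly larger evaluable number. The understated standard error is not repaired by either. Because it affects the primary test and interval and costs little to correct, it should be changed.

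**What to change.** 1. Record, for each intervention participant, the education group attended. This comes first, since no adjustment is possible without it.
2. Make the primary comparison allow for clustering in the intervention arm only, with controls and intervention participants who never attended each treated as a singleton. Two routes are acceptable: a partially nested mixed model with small-sample degrees of freedom, or cluster-robust standard errors with a small-sample correction. Choose one before the outcome data are seen.
3. Restate power as a range under stated analysed group sizes and ICCs, and say whether 5.3 mg is a residual SD, so that any credit for baseline adjustment is visible.

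Recruitment stays at 290. The cost is one recorded variable, revised analysis wording, a slightly wider interval and a slightly less favourable power statement.

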### Data analysis

A Consolidated Standards of Reporting Trials (CONSORT) study flowchart will detail the movement of participants throughout the PACES study [52]. Baseline descriptive characteristics will be summarised by treatment arm. Continuous variables will be expressed as mean values (and SDs), or median values (with lower and upper quartiles) where appropriate. Binary and categorical variables will be expressed as number (percentage). Data will be checked for parametric assumptions. A complete case population (i.e. those with complete data for the primary outcome) will be analysed as the primary analysis.

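### The complete-case change score drops randomised participants who have a valid 12-month accelerometer file but a failed baseline wear

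*Protocol article*

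**What the plan says.** All places are in the Methods of the protocol article.

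- **Sample size.** The calculation concerns change in average daily activity (ENMO, in mg) from baseline to 12 months. The inputs are "In order to detect a minimum clinically significant difference of 2.1 mg", "assuming a standard deviation (SD) of 5.3 mg" and "a power of 80% and significance level of 5%, the sample size requires 202 participants". It then adds: "To allow for 20% loss to follow-up and 10% non-compliance of the activity monitor, 290 participants will be recruited to this trial".
- **Data analysis.** "A complete case population (i.e. those with complete data for the primary outcome) will be analysed as the primary analysis". No exception is stated for participants who lack only the baseline file.
- **Primary outcome data processing and data analysis.** A file is excluded for excessive calibration error or if "fewer than 4 days of 16 h of wear-time were recorded by the monitor". The regression adjusts for baseline activity and for the change in wear-time. Imputation of missing data is listed among the sensitivity analyses.
- **Primary outcome.** The monitor is worn for eight days, "wearing the monitor from the date of the assessment visit", and posted back afterwards.
- **Randomisation.** "Upon completion of visit 1, participants are randomised using a 1:1 block design". Participants learn their allocation once that visit is over. No valid baseline wear is required first.

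**The concern.** The outcome and two covariates (baseline activity and change in wear-time) all need the baseline file. That file does not exist when the participant is randomised, because its eight days of wear begin at the visit that randomisation closes. A poor baseline wear is thus a loss after randomisation, not a screening failure.

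Two things are at stake. Participants who supplied a good 12-month measurement are discarded, which costs precision. The primary analysis set also moves further from everyone randomised, through an event that follows allocation. Neither depends on how the 10% monitor allowance is read.

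The allowance raises a related question. It is given once, without saying whether it describes each wear or the pair, so it is worth checking whether 290 still supports the stated power.

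**Working it through.** **1. The plan's own figures.** The standardised difference is 2.1/5.3 = 0.396. A two-sided 5% t-test with 80% power needs 100.96, so 101, per arm, or 202 in total. With the allowances added, 202/(1 − 0.20 − 0.10) = 202/0.70 = 288.6, taken up to 290. Both figures reproduce. Conversely, 290 × 0.70 = 203, with 80.2% power.

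**2. Who is dropped for a failed baseline alone.** The documents give no failure rate per wear and no correlation between wears. As an assumption, take f = 10% per wear, with 20% lost to follow-up.

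| How failures fall | Valid 12-month file | Valid pair | Dropped for baseline only |
|---|---|---|---|
| Independent | 290 × 0.8 × 0.9 = 209 | 290 × 0.8 × 0.9 × 0.9 = 188 | 21 |
| Losses never overlap | 290 × (1 − 0.2 − 0.1) = 203 | 290 × (1 − 0.2 − 0.1 − 0.1) = 174 | 29 |
| Same people fail both wears | 290 × 0.8 × 0.9 = 209 | 209 | 0 |

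Suppose instead that 10% is the combined figure and failures are independent. Then f = 1 − √0.90 = 5.1% per wear, and 290 × 0.8 × 0.949 × 0.051 = 11 participants are dropped for baseline alone.

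**3. What keeping them is worth.** In the independent 10% case the standard error falls by at most 1 − √(188/209) = 5%. This is an upper bound, since a participant with an imputed baseline carries less information than one with an observed baseline.

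**4. Power of an unadjusted t-test on the valid pairs.**

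| Reading of the 10% | Analysable | Power |
|---|---|---|
| Share without a usable pair | 203 | 80.2% |
| Per wear, independent | 188 | 77.1% |
| Per wear, never overlapping | 174 | 73.9% |
| Per wear, same people | 209 | 81.3% |

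The per-wear failure that still leaves 202 is 1 − √(202/232) = 6.7% if independent, (0.8 − 202/290)/2 = 5.2% if never overlapping, and 1 − 202/232 = 12.9% if the same people fail both.

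**5. Power of the planned model.** The plan adjusts for baseline activity. If 5.3 mg is the SD of change (an assumption) and variances are equal at both times, adjustment multiplies the variance by (1 + ρ)/2, where ρ is the baseline to 12-month correlation. With 188 analysed, power is 88%, 83% and 81% at ρ = 0.5, 0.7 and 0.8, and stays at 80% or more up to ρ of about 0.86. With 174 it does so up to about 0.72.

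**6. Changing the outcome does not change the question.** With baseline activity as a covariate, regressing change or the 12-month value on arm gives the same arm coefficient in the same participants: subtracting baseline from the outcome shifts only the coefficient of baseline. Moving to the 12-month value therefore costs nothing in interpretation and turns a missing baseline into a missing covariate.

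**The case against.** **On power.** A reader might infer that 290 recruits deliver 80% power only if about 5–7% of wears fail. The documents do not support that. The natural reading of the allowance, in a calculation about change, is the share of participants without a usable pair, and then the plan's numbers agree. The 5–7% limit needs failures that are independent or never overlap, while non-compliance may well cluster in the same people. The 77% and 74% figures also belong to an unadjusted test that is not the planned one. This objection stands, and the sample size is not charged with an error.

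**On timing.** The recruitment section places baseline measurements before randomisation, Table 1 lists the accelerometer among them, and the flowchart is not shown. But the wear starts at the visit and lasts eight days, and no section makes its success a condition of randomisation. The order described here is the plain reading.

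**On differential loss.** Because baseline wear follows allocation, a reader might infer that exclusions differ by arm. That is possible, but nothing in the documents shows it.

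**On existing safeguards.** The intention-to-treat analysis with multiple imputation would bring these participants back. That is true, but only as a sensitivity analysis; the primary estimate still omits them.

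**Conclusion.** The point holds for the analysis set. However the 10% is read, the primary analysis excludes any randomised participant whose baseline file fails, including those with a valid 12-month file. On the assumptions above this is about 11 people if 10% is a combined rate with independent failures. At 10% per wear it is about 21 (0 to 29, depending on overlap), and recovering the 21 would reduce the standard error by at most about 5%. The true number is unknown, because no failure rate is given.

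This is an inexpensive improvement in precision and in keeping to the randomised groups. It does not show bias, and it does not show a wrong sample size. Whether the 10% is per wear or combined is a missing definition. On the combined reading 80% power is met. On the per-wear reading the unadjusted figure ranges from 74% to 81%, and baseline adjustment could restore 80%.

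**What to change.** 1. Make 12-month ENMO the primary outcome, compared between arms with adjustment for the stratification factors and baseline ENMO. Impute missing baseline ENMO by a method fixed in advance, so that everyone randomised with a valid 12-month file contributes.
2. The change in wear-time also needs the baseline file. Drop it from the primary model or handle its missing values in the same way; otherwise the same participants are lost again.
3. A longitudinal model that also uses the 6-month accelerometer data is an option. Its usual assumption of a common baseline mean should be checked, because baseline wear follows allocation and participants may know their arm while wearing the monitor.
4. Add one sentence to the sample size section saying whether the 10% applies to each wear or to the pair.

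The cost is slightly more analysis work and some reliance on the baseline imputation model. The complete-case analysis can be kept as a sensitivity analysis to show how much rests on it. No extra participants, visits or measurements are needed.
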